### Sample Size

We calculated the sample size based on the primary outcome of MBI scores, which is evaluated at recruitment and at 4, 8, and 12 weeks. The historical mean of the MBI is 73 (SD 25). The study aims to detect a difference of 5 points between the control and intervention groups assuming a correlation of 0.35 between the repeated measurements. The sample size estimated to detect this difference with 80% power and a 5% significance level is 175 participants per group assuming equal allocation between arms. After accounting for 20% attrition, the total sample size required for the study is 450.

### Recruitment and Screening

Participants will be recruited from the inpatient wards of 3 CHs, namely Outram Community Hospital, Sengkang Community Hospital, and Jurong Community Hospital. Each site will recruit 150 patients (75 in the intervention group and 75 in the control group), with a total of 450 participants recruited across all 3 sites.

The participants will first be screened by their ward therapists for eligibility, after which a member of the research team will approach them to provide information about the study as well as to take informed consent. Study team members will also provide reminders to ward therapists during their regular roll calls to maximize recruitment efforts.

### Randomization and Blinding

Participants will be randomized to the intervention or control group based on a 1:1 allocation ratio. Stratified block randomization with randomly varying block sizes will be implemented with recruitment site as the stratification factor.

After taking informed consent, the research coordinator will contact a member of the team (who oversees the progress but is not involved in patient recruitment) to obtain the randomized assignment. The research coordinator will remain blinded to the allocation prior to contacting the team member. Due to the nature of the intervention, blinding of study participants will not be possible.

### Statistical Analyses

Participants will be analyzed via an intention-to-treat approach. Participant characteristics will be summarized using median (IQR) or mean (SD) for nonnormally distributed and normally distributed data, respectively, and count and percentage for categorical variables.

Linear mixed-effects model will be used to assess the pattern of change in the primary outcome of the MBI score and secondary outcomes of EQ-5D, 5-time chair stand test (5CST), and joint range over the 12-week follow-up period. A uniform correlation structure will be specified to model the within-subject correlation of these repeated measures. MBI, EQ-5D, 5CST, and joint range of motion will be treated as continuous outcomes. Normality of continuous outcome variables will be assessed through visual inspection methods. If normality assumptions are met, parametric methods will be used; otherwise, a suitable transformation may be performed to address the issue of nonnormality.

As individuals of different age groups have varying body composition, functional capacity, and physiological reserves, there may be differential influences on baseline functional ability and recovery trajectories. To ensure that any potential age-related differences are accounted for, we will first assess the interaction between the age category, treatment groups, and duration of time. We will stratify into age categories, and if statistically meaningful effect modification by age is observed, an age-stratified analysis will then be conducted.

Poisson regression will be used to compare length of stay between intervention and control groups. If there is evidence of overdispersion and/or zero inflation, negative binomial regression or corresponding zero-inflated models will be implemented instead.

Key prognostic factors such as baseline MBI, RDG grouping, and time will be adjusted a priori. The secondary outcome based on 30-day readmission will be compared between the intervention and control group using modified Poisson regression. The effect estimate will be quantified in terms of relative risk and its 95% CI.

For both the primary and secondary outcomes, linear mixed-effects model on the log-transformed scale will be applied if the model assumptions are violated.

Missing data are expected due to the nature of the study and will be handled by imputation.

The preferred method of imputation will be applied accordingly based on the degree of missingness, such as last observation carried forward.

The cost-effective analysis will evaluate both direct cost savings and cost-effectiveness in terms of quality-adjusted life years (QALYs). To assess direct cost savings, the analysis will evaluate the difference in length of stay at the hospital between the intervention and control group (Table 4). The results will be expressed as mean cost differences between groups. Cost per QALY gained will be evaluated for the cost-effectiveness of the intervention. QALY will be derived using EQ-5D-5L utility scores, and incremental cost-effectiveness ratios (ICERs) will be calculated. The ICERs will be compared to established willingness-to-pay thresholds to determine the cost-effectiveness of the intervention. Sensitivity analyses will be performed to account for uncertainties in cost and QALY estimates. Results will be presented using cost-effectiveness planes and acceptability curve.

**Table 4 table4:** Cost-accounting for the cost-effectiveness analysisa.

Cost category	Cost type	Cost item	Unit of measurement	Source of unit cost	Applicable to
Hardware	Direct	Rebee kits	Per kit per day	Research collaboration agreement	Intervention
Software	Direct	Rebee subscription	Per patient per day	Research collaboration agreement	Intervention
Inpatient care	Direct	Average length of stay	Per patient per day	Electronic medical records	Control and intervention
Manpower	Direct	CRC’s^b^ daily EOM^c^	Per day	Human resource	Intervention

^a^The statistical analysis will be conducted using R (R Foundation for Statistical Computing). All evaluations will be made using 2-side *P* values at the 5% level of significance.

^b^CRC: clinical research coordinator.

^c^EOM: expenditure of manpower.

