### Outcome Measures

The primary outcome is functional status measured over 12 weeks. Functional status will be measured using modified Barthel index (MBI), a 100-point ordinal scale for the assessment of a patient’s functional state. The MBI assesses activities of daily living over 10 domains comprising transfers, ambulation, stair climbing, bathing, dressing, toileting, bowel control, bladder control, personal hygiene, and feeding [29].

Secondary outcomes include physical performance, quality of life, length of stay in CH, 30-day readmission rates, and cost-effectiveness over 12 weeks. Patients who are admitted under RDG total knee replacement will have an additional outcome measure of joint range. The outcome measures as well as the method of measurement are listed in Table 3. Health care cost will be calculated from electronic medical records and supplemented with survey data regarding the number of DRC or home therapy sessions attended, manpower hours to train patients to use Rebee, costs of Rebee software and hardware, and use of outpatient community services (eg, day care center, home nursing, housekeeping, and meals on wheels). The tools to be used in this study to measure the outcomes are validated and implemented in routine clinical care.

**Table 3 table3:** Primary and secondary outcome measures.

Variables			Data source, method of measurement, and definitions		Time points
Primary outcome					
	Functional status	Survey: MBI^a^. To establish the degree of independence from any help. A score from 0- 100 using the MBI questionnaire, with 100 being fully ambulant without any help.		Baseline and 4, 8, and 12 weeks	
Secondary outcomes					
	Joint range	Measurement using goniometer on affected knee. Active and passive range of motion (flexion and extension) of affected knee.		Baseline and 4, 8, and 12 weeks	
	Physical performance	Measured by performing 5CST^b^. Measures the time taken to complete 5 sit to stands (in seconds)		Baseline and 4, 8, and 12 weeks	
	Quality of Life	Survey: EQ-5D-5L		Baseline and 4, 8, and 12 weeks	
	Length of stay	Electronic medical records		Date of discharge from CH^c^ minus date of randomization	
	30-day readmission rates	Electronic medical records		12 weeks	
	Direct health care cost	Electronic medical records: cost of inpatient stay		12 weeks	
	Direct health care cost	CRC’s^d^ daily expenditure of manpower		4, 8, and 12 weeks	
	Direct health care cost	Rebee costs: software and hardware		12 weeks	

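### The fixed uniform within-patient correlation can understate standard errors for time-by-arm contrasts, and the plan names no alternative structure or robust standard error

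*Protocol article*

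**What the plan says.** The relevant text is in the protocol article, under Outcome Measures, Sample Size and Statistical Analyses.

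- **Outcome:** "The primary outcome is functional status measured over 12 weeks". MBI is "evaluated at recruitment and at 4, 8, and 12 weeks".
- **Model:** "Linear mixed-effects model will be used to assess the pattern of change in the primary outcome of the MBI score". The same model serves EQ-5D, 5CST and joint range.
- **Covariance:** "A uniform correlation structure will be specified to model the within-subject correlation of these repeated measures".
- **Covariates:** "Key prognostic factors such as baseline MBI, RDG grouping, and time will be adjusted a priori".
- **Interaction:** a three-way interaction of age category, treatment group and time is assessed first. Its result decides whether an age-stratified analysis is run.
- **Fallback:** "linear mixed-effects model on the log-transformed scale will be applied if the model assumptions are violated". A suitable transformation is also allowed for non-normality. Neither changes the correlation structure, and no robust standard error is mentioned.
- **Planning figures:** one SD (25) and one correlation (0.35) for all visits. "The study aims to detect a difference of 5 points between the control and intervention groups".

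**The concern.** A uniform structure (compound symmetry) gives every visit the same variance and every pair of visits the same correlation. There are reasons to doubt both here. Baseline is taken in hospital, and stays last about 3 to 4 weeks, so later visits mostly follow discharge. The MBI stops at 100, about one SD above the historical mean of 73, so the spread may change as patients improve. Correlation between visits 12 weeks apart may also be lower than between visits 4 weeks apart.

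If so, the model uses the wrong standard error for contrasts within patients over time. The plan calls for such contrasts twice: in the pattern of change, and in the interaction that decides on age-stratified analysis. A false signal in the latter would open subgroup analyses more often than the nominal 5% implies.

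**Working it through.** **1. The plan's own figure.** Take baseline as a covariate, three follow-ups and uniform correlation 0.35. The variance factor is (1 + 2×0.35)/3 − 0.35² = 0.5667 − 0.1225 = 0.4442. Then n = 2 × (1.960 + 0.842)² × 25² × 0.4442 / 5² = 174.3, that is 175 per group, as stated. Other readings do not fit: the mean of four visits gives 202, the mean of three follow-ups without baseline 223, a change score 341, single-visit ANCOVA 345, and a slope 460. The powered contrast is therefore the baseline-adjusted average over follow-up.

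**2. Method.** With complete, balanced data and a large sample, let R be the true variance of a contrast divided by the variance that the uniform model assigns to it. The uniform model uses the average variance and the average covariance. Type I error at nominal 5% is 2 × [1 − Φ(1.96/√R)]. All true covariances below are assumptions.

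**3. Linear time-by-arm contrast, all four visits as outcomes, equal variances.** Let r1, r2, r3 be the correlations at 4, 8 and 12 weeks apart. With weights (−3, −1, 1, 3), the true variance is proportional to 20 + 10r1 − 12r2 − 18r3. The model variance is proportional to 20 × (1 − mean r), with mean r = (3r1 + 2r2 + r3)/6.
- Correlations 0.50/0.35/0.20: 17.2 / 12.0 = 1.43, giving 10.2%.
- Decay of 0.75 per 4 weeks: 13.16 / 7.34 = 1.79, giving 14.3%.
- Uniform 0.35: R = 1, giving 5.0%.
- First-order autoregressive (AR(1)) decay from 0.35 to 0.9 per 4 weeks: 9.4% to 16.0%. Simulation with 175 per arm and 4,000 runs agreed over 0.35 to 0.8 (9.1% to 15.2%).

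**4. Same contrast, baseline as covariate, weeks 4, 8 and 12 as outcomes.** With one baseline coefficient and weights (−1, 0, 1), R = (1 − r2)/(1 − mean r), with mean r = (2r1 + r2)/3.
- 0.50/0.35/0.20: 0.65/0.55 = 1.18, giving 7.1%.
- AR(1) at 0.496, which keeps the four-visit average at 0.35: 0.754/0.587 = 1.28, giving 8.4%.
- Decay 0.75: 0.4375/0.3125 = 1.40, giving 9.8%.

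Visit-specific baseline coefficients give 6.7%, 7.9% and 9.1% for the same cases.

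**5. Age-by-treatment-by-time interaction.** This was simulated with 407 patients, two assumed age groups, linear time, no true effect and 4,000 runs.
- Four visits as outcomes: 10.5% (0.50/0.35/0.20), 14.5% (decay 0.75), 4.6% (true uniform 0.35).
- Baseline as covariate: 6.5%, 8.6% and 9.5% for AR(1) 0.35, 0.50 and 0.75.

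**6. Week-12 difference.** With four outcomes and equal variances it keeps 5.0% under any correlation. With baseline as covariate, decaying correlation gives 6.3% (0.50/0.35/0.20) and 8.2% (decay 0.75). Unequal SDs with uniform correlation give the following.

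| SD at the four visits | Four outcomes | Baseline as covariate |
|---|---|---|
| Rising 16, 19, 22, 25 | R = 625/431.5 = 1.45; 10.3% | R = 625/490 = 1.28; 8.3% |
| Falling 25, 22, 19, 16 | R = 256/431.5 = 0.59; 1.1% | R = 256/367 = 0.70; 1.9% |

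The denominators are the mean squared SDs over the visits used as outcomes.

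**7. Average over visits.** R = 1 in every scenario, so type I error stays at 5.0%.

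**The case against.** The strongest defence is that the powered comparison is safe. The sample size reproduces as an average effect over follow-up, which keeps its level under any covariance when data are complete. A uniform structure is a common, pre-specified choice, and the only planning figures (one SD, one correlation) agree with it. If it is true, every contrast keeps 5%. Degrees-of-freedom methods are normally left to the analysis plan, which is not shown. All of this stands, and it limits the point.

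Three stronger readings are tempting but not supported:

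- **That the primary test runs at 10-15%.** That range needs an assumed decay and all four visits as outcomes, whereas the article adjusts for baseline MBI. It also applies to a slope, which the article does not name as the primary test. An omnibus group-by-time test is much less affected: 5.1-5.6% with baseline as covariate in the scenarios examined.
- **That week-12 standard errors are generally too small.** A ceiling would be expected to compress the spread, and a falling SD makes the test conservative.
- **That dropout biases the estimates through the wrong covariance.** The plan imputes missing values, so the model would be fitted to completed data. Whether that imputation is sound is a separate question.

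The defence does not remove the interaction test, which is a planned within-patient contrast. Nor is the structure a detail left open: the article fixes it.

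**Conclusion.** The point holds in conditional form, as a cheap improvement. The one covariance rule that the plan states is correct only if variance and correlation are constant across visits, and the plan provides nothing to protect inference if they are not. The inflation ranges describe what plausible decay would do to time-by-arm slopes and to the age interaction. They are not estimates for this trial, because no visit-specific SD or correlation is reported. The direction for week 12 is unknown. The calculations assume complete, balanced data and large-sample tests. Nothing here undermines the stated sample size or the average treatment effect.

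**What to change.** In Statistical Analyses, replace the uniform structure with an unstructured covariance (visit-specific variances and correlations), fitted by REML with Kenward-Roger or Satterthwaite degrees of freedom, for MBI, EQ-5D, 5CST and joint range. If that model does not converge, keep the uniform structure and use patient-clustered robust standard errors. In large samples either route restores about 5% for every contrast above, and little is lost if the uniform structure is true.

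The cost is one sentence and a few parameters: 4×5/2 = 10 with four visits as outcomes, or 3×4/2 = 6 with three, instead of 2. That is negligible with 407 recruited participants. Joint range is measured only in the total knee replacement subgroup and may need the fallback. The article reports that analysis is under way, so the change should be dated and recorded before arm-level results are examined. If they have already been examined, report the revised model alongside the stated one.

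### Normality is judged on the raw outcomes rather than on the mixed-model residuals, and an unreconciled second rule can also move the primary analysis off the MBI points scale without need

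*Protocol article*

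**What the plan says.** All the analysis wording is in the Statistical Analyses section of the protocol article.

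- **Primary model:** "Linear mixed-effects model will be used to assess the pattern of change in the primary outcome of the MBI score", with the other continuous outcomes treated the same way.
- **Adjustment:** "Key prognostic factors such as baseline MBI, RDG grouping, and time will be adjusted a priori".
- **Check:** "Normality of continuous outcome variables will be assessed through visual inspection methods". The sentence just before it lists these variables as MBI, EQ-5D, the chair stand test and joint range of motion.
- **Consequence of the check:** "If normality assumptions are met, parametric methods will be used; otherwise, a suitable transformation may be performed to address the issue of nonnormality".
- **Second rule, some paragraphs later, for primary and secondary outcomes:** "linear mixed-effects model on the log-transformed scale will be applied if the model assumptions are violated".

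Residuals and random effects are not mentioned. Elsewhere, Outcome Measures describes the MBI as "a 100-point ordinal scale for the assessment of a patient’s functional state", and Sample Size plans to "detect a difference of 5 points between the control and intervention groups assuming a correlation of 0.35 between the repeated measurements", so the trial was designed on untransformed points.

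**The concern.** A linear mixed model makes no assumption about the marginal distribution of the outcome. It assumes that residuals and random effects are roughly normal once the covariates are in the model. Baseline MBI, diagnostic group and time are exactly the things that can give the raw MBI an irregular shape, and the model already accounts for them. A plot of the raw outcome can therefore look non-normal when the model is adequate, and it does not show directly whether the residuals are acceptable.

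The check also has a consequence. It permits a change of scale for the primary outcome, of unstated form, chosen after outcome data have been seen in a trial that Study Design calls unblinded. The log-scale rule adds a second route off the points scale. The visual-check rule is optional and open as to the transformation; the log-scale rule is mandatory and fixes the transformation but not the diagnostic. An analyst cannot tell which governs.

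At stake are the interpretability of the primary result against the 5-point target and, for a log transformation, some power.

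**Working it through.** **1. The design scale.** Inputs from Sample Size: difference 5, SD 25, correlation ρ = 0.35, power 80%, 5% significance; two-sided testing is stated in the note to Table 4. Three follow-ups (4, 8 and 12 weeks) and one baseline.

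- Single-measurement size per group: 2 × [25 × (1.960 + 0.842) / 5]² = 392.4.
- Factor for the mean of r = 3 follow-ups adjusted for baseline: (1 + 2ρ)/3 − ρ² = 1.70/3 − 0.1225 = 0.4442.
- 392.4 × 0.4442 = 174.3, rounded up to **175 per group**, the stated figure.

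The calculation thus rests on a baseline-adjusted comparison of untransformed points. Any transformation leaves that scale.

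**2. Number available.** Results gives 407 recruited. With the planned 20% attrition, 407 × 0.8 / 2 = 162.8, or about 163 per arm. The standard error is 25 × √(2 × 0.4442/163) = 1.846. Before any ceiling effect, power at 5 points is Φ(5/1.846 − 1.960) = Φ(0.749) ≈ 77%.

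**3. Would the raw and residual checks disagree?** The ceiling lies (100 − 73)/25 = 1.08 SD above the historical mean of 73, so skewness is likely in both. I simulated scores with SD 25 and uniform correlation 0.35 on a latent scale, clipped them to 0–100, and used 163 per arm. The latent mean of 76 is an assumption; it gives an observed mean of about 74 and an observed SD of about 21. No diagnostic-group effect was included, because the documents give none.

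- Skewness with no treatment effect: raw −0.60, residuals −0.54.

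Here the ceiling drives both, and inspecting residuals instead of raw values would change little.

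Case mix can separate the two, but the size is bounded by the plan's own correlation. If all between-patient variance (0.35 × 625 = 218.75) came from an assumed 70/30 mix of two groups, the gap would be √(218.75/0.21) = 32.3 points. The raw skewness would be −0.084 × 32.3³ / 25³ ≈ −0.18, which few readers would notice by eye.

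**4. Is leaving the points scale needed, and what does it cost?** Same simulation, comparing arms on the mean of the three follow-ups adjusted for baseline. The log analysis uses log(MBI+1); the +1 is assumed because the scale includes 0.

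| | Untransformed MBI | log(MBI+1) |
|---|---|---|
| Type I error | 5.1% to 5.5% over two runs | 5.2% |
| Power, 5-point latent shift | about 74% | about 66% |

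The untransformed test keeps its size despite skewed residuals. The log moves the skewness the wrong way, from −0.60 to about −3.0, because the MBI is left-skewed. A 5-point latent shift appears as about 4 points after clipping, so the comparison between the columns matters more than either absolute value.

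**The case against.** **The log-scale sentence already refers to model assumptions.** For a mixed model that would ordinarily mean residuals and random effects, and the visual-check sentence only permits a transformation. This stands in part: the visual check alone does not decide the scale of the primary analysis. But the log-scale sentence names no diagnostic and does not withdraw the check on the outcomes, which is the only normality check described.

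**A journal article condenses, and the wording may be loose shorthand.** Which plots are drawn can be left to an analysis plan. The object of the check and its consequence, however, are stated here, and they are stated for the wrong quantity.

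**For the MBI the target of the check hardly matters.** This largely stands, as step 3 shows. It makes keeping the points scale the more useful half of the fix.

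**Stronger readings that the documents do not support.**

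- A reader might infer that raw MBI is bound to look non-normal while the residuals look fine. A formal normality test can show a stark contrast in simulations with widely separated subgroups, but those conflict with Sample Size. An 80/20 mix 50 points apart has between-group variance 0.16 × 2500 = 400, and 400/625 implies a within-patient correlation of at least 0.64 against the planned 0.35. A formal test on hundreds of values is also far more sensitive than the eye.
- A reader might infer that the type I error is inflated. That would require picking the more favourable of two analyses. The protocol describes no such practice, and each scale alone holds close to 5%.

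**Conclusion.** The point holds, at minor to moderate severity. The stated normality check looks at the raw outcomes, whereas the planned model concerns residuals and random effects, and two unreconciled rules can move the primary analysis off the scale on which the trial was sized. That conclusion rests on the text and on what the model assumes, not on simulation.

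The frequency of a needless move cannot be given, because case mix is not reported and the ceiling will probably skew the residuals as well. The cost, if the move is to the log, is about 8 percentage points of power at the target difference (74% to 66%). The untransformed analysis shows no type I error problem that would justify the move. These figures depend on the assumed latent mean of 76, clipping at 0 and 100, a constant treatment shift on the latent scale, the +1 offset, and attrition of 20% from the 407 recruited.

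**What to change.** Replace the visual-check rule and the log-scale rule with one, for example: *Assumptions will be assessed on the residuals and predicted random effects of the prespecified mixed model, using QQ and residual-versus-fitted plots, by someone blind to arm. The model for untransformed MBI remains the primary analysis whatever the plots show. If residuals are clearly non-normal, robust or participant-level bootstrap standard errors will be used on the same scale. Any transformed analysis is a sensitivity analysis.*

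The cost is a short, dated wording change in the analysis plan. It needs no new data and leaves the sample size as it is. The Results section says that data collection is complete and analysis is under way, so the change should be made before the treatment comparison is examined. If outcome plots have already been inspected, the report should say so.

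### Randomization is stratified by recruitment site, but no analysis model names site, so the standard errors as written are conservative and some precision is lost

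*Protocol article*

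**What the plan says.** Under Randomization and Blinding, the Protocol article states: "Stratified block randomization with randomly varying block sizes will be implemented with recruitment site as the stratification factor". Recruitment and Screening plans 150 patients at each of three community hospitals, 75 per arm.

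Under Statistical Analyses, the covariates are described in one sentence: "Key prognostic factors such as baseline MBI, RDG grouping, and time will be adjusted a priori". MBI, EQ-5D, the chair stand test and joint range are to be analysed with a linear mixed-effects model, for which "A uniform correlation structure will be specified to model the within-subject correlation of these repeated measures". Length of stay is to be compared by Poisson regression, with negative binomial or zero-inflated models as alternatives, and 30-day readmission by modified Poisson regression. Site is not named in any of these models, either as a fixed or as a random effect.

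Age is treated separately. The section says of age that "there may be differential influences on baseline functional ability and recovery trajectories" and that "we will first assess the interaction between the age category, treatment groups, and duration of time", followed by an age-stratified analysis if effect modification is seen.

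**The concern.** Blocked allocation within each hospital keeps the two arms close to equal in size at every site. Outcome differences between hospitals then largely cancel from the treatment contrast, so the true sampling variance of that contrast does not contain them. A model without a site term still counts those differences as unexplained variation between patients. It reports a standard error larger than the real one, confidence intervals that are too wide, and a test that rejects less often than 5% under the null.

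What is at stake is calibration and precision. Recruitment closed at 407 against a target of 450, so precision that can be had from the design at almost no cost is worth taking. The Results section also says that analysis is under way, so the covariate set should be settled in writing before the arms are compared. Length of stay feeds the direct cost-savings comparison as well, so its precision carries into the economic result.

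**Working it through.** **Inputs from the article (Sample Size).** SD 25; 80% power; 5% significance level (two-sided, from the note to Table 4); one baseline and three follow-up measurements. The aim is to "detect a difference of 5 points between the control and intervention groups assuming a correlation of 0.35 between the repeated measurements". Stated result: 175 per group, 450 in total.

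**Input not in the article.** The between-site share s of the residual outcome variance. It is assumed here, with 2%, 5% and 10% as the range.

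**Step 1: reproduce the planned sample size.** For the mean of three follow-ups adjusted for one baseline under uniform correlation, the variance factor is

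(1 + 2 × 0.35)/3 − 0.35² = 0.5667 − 0.1225 = 0.4442.

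Without that factor, n = 2 × (1.960 + 0.8416)² × 25²/5² = 392.4 per arm. With it, 392.4 × 0.4442 = 174.3, which rounds up to the stated 175. No site term is needed to reach this figure. Allowing for 20% attrition, 175/0.8 rounds up to 219 per arm, or 438 in total; 450 is close to this and equals 3 × 150.

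**Step 2: standard errors.** The residual SD of the adjusted follow-up mean is 25 × sqrt(0.4442) = 16.66. At 175 per arm, the model SE without site is 16.66 × sqrt(2/175) = 1.781. The true SE under allocation balanced by site is 1.781 × sqrt(1−s). The ratio of model SE to true SE is therefore 1/sqrt(1−s).

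**Step 3: type I error and power.**
- Type I error, site omitted: 2 × Φ(−1.96/sqrt(1−s)).
- Power, site omitted: Φ((5 − 1.96 × model SE)/true SE).
- Power, site included: Φ(5/true SE − 1.96).

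For s = 5%, the true SE is 1.781 × 0.9747 = 1.736. Power with site omitted is Φ((5 − 3.491)/1.736) = Φ(0.869) = 80.8%. With site included it is Φ(2.880 − 1.96) = Φ(0.920) = 82.1%.

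| Assumed s | SE too large by | True type I error | Power, site omitted | Power, site included | Difference (points) |
|---|---|---|---|---|---|
| 0 | 0% | 5.0% | 80.2% | 80.2% | 0 |
| 2% | 1.0% | 4.8% | 80.4% | 80.9% | 0.5 |
| 5% | 2.6% | 4.4% | 80.8% | 82.1% | 1.3 |
| 10% | 5.4% | 3.9% | 81.4% | 84.1% | 2.7 |

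**Step 4: simulation check.** Three sites of 116 patients (348 analysed), blocks of 4, one adjusted score per patient with SD 16.66, 10,000 runs per setting. At s = 5%, type I error was 4.5% without site and 5.1% with it, and power 79.5% and 81.0%. At s = 10%, type I error was 3.9% and 4.9%, and power 81.8% and 84.5%. Both agree with the formulas to within simulation error.

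The calculation concerns the between-arm difference averaged over follow-up, the contrast that reproduces the sample size. The size for length of stay and readmission was not computed, because the article gives no variance figures for them.

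**The case against.** **The list is open.** The covariate sentence introduces its examples with *such as*, the document is a condensed article, and a SAP that is not shown may list site. This stands as a limit on confidence: a reader might infer that the plan restricts adjustment to the three named factors, and the text does not say that. But the article did choose to state factors fixed in advance, and the one variable that its own randomization calls for is not among them. An open list does not put site in the model.

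**The error is on the safe side.** This stands in full. There is no bias and no excess of false positives.

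**The size is assumed.** This also stands. Adjustment for baseline MBI and RDG grouping may absorb part of any difference between hospitals. An s of 10% would need a between-site SD of sqrt(0.10) × 16.66 = 5.3 MBI points after that adjustment, more than the 5-point target difference, so it belongs at the upper end of the range.

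**Power need not fall below 80%.** A reader might infer that omitting site takes the trial below its planned power. The article does not describe the SD of 25 as a within-site figure, and 175 per arm is reproduced without a site term, so on the plan's own terms the loss is a forgone gain. If the SD were nevertheless read as applying after site adjustment, power with site omitted would be Φ(2.8016 − 1.96/sqrt(1−s)), or about 79.4%, 78.5% and 76.9%. Even then, s = 10% costs about 7% of the sample, since (2.6956/2.8016)² = 0.926, not one patient in ten.

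**Age is a different matter.** A reader might see the absence of age from the named covariates as the same fault. It is not. Age is not a stratification factor, so leaving it out cannot make the standard errors disregard the design, and age already enters through the interaction analysis.

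**Conclusion.** The point holds as an omission in the analysis as written: the only stratification factor appears in no model. The consequence is conservative inference and a modest loss of precision. For an assumed s of 2% to 10%, standard errors are 1.0% to 5.4% too large, type I error is about 4.8% to 3.9%, and power is 0.5 to 2.7 points lower than with site included at 175 per arm. If s is near zero, nothing of note is lost.

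The direction follows from the stated design whenever sites differ in outcome. The size rests on the assumed s and on near-equal arms within each site. A reader might also infer a larger effect on length of stay through differing discharge practice between hospitals. That is plausible, but the article gives no figure to support or size it. The change is worth making because it is nearly free; the validity of the treatment effect estimate does not depend on it.

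**What to change.** Name recruitment site, as a three-level fixed effect, in the primary MBI model and in every secondary outcome model, including those for length of stay and 30-day readmission. State the full covariate set as a closed list. The cost is one line of model specification and two degrees of freedom with 407 patients recruited.

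Because analysis is already under way, record the change with a date before the arms are compared. If that comparison has already been run, report the site-adjusted result beside it and say when each was specified.

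Adding age as a main-effect covariate is optional. It could bring a gain in precision (at an assumed 5% of residual variance explained, power rises from 80.2% to 82.1% at 175 per arm), but it is not part of correcting for the stratified design.
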